## Abstract

**Background:**

Spinal metastases can lead to unremitting pain and neurological deficits, which substantially impair daily functioning and quality of life. Patients with unstable spinal metastases receive surgical stabilization followed by palliative radiotherapy as soon as wound healing allows. The time between surgery and radiotherapy delays improvement of mobility, radiotherapy-induced pain relief, local tumor control, and restart of systemic oncological therapy. Stereotactic body radiotherapy (SBRT) enables delivery of preoperative high-dose radiotherapy while dose-sparing the surgical field, allowing stabilizing surgery within only hours. Patients may experience earlier recovery of mobility, regression of pain, and return to systemic oncological therapy. The BLEND RCT evaluates the effectiveness of SBRT followed by surgery within 24 h for the treatment of symptomatic, unstable spinal metastases.

**Methods:**

This phase III randomized controlled trial is embedded within the PRospective Evaluation of interventional StudiEs on boNe meTastases (PRESENT) cohort. Patients with symptomatic, unstable spinal metastases requiring stabilizing surgery and radiotherapy will be randomized (1:1). The intervention group (*n* = 50) will be offered same-day SBRT and surgery, which they can accept or refuse. According to the Trial within Cohorts (TwiCs) design, the control group (*n* = 50) will not be informed and receive standard treatment (surgery followed by conventional radiotherapy after 1–2 weeks when wound healing allows). Baseline characteristics and outcome measures will be captured within PRESENT. The primary outcome is physical functioning (EORTC-QLQ-C15-PAL) 4 weeks after start of treatment. Secondary endpoints include pain response, time until return to systemic oncological therapy, quality of life, local tumor control, and adverse events up to 3 months post-treatment.

**Discussion:**

The BLEND RCT evaluates the effect of same-day SBRT and stabilizing surgery for the treatment of symptomatic, unstable spinal metastases compared with standard of care. We expect better functional outcomes, faster pain relief, and continuation of systemic oncological therapy. The TwiCs design enables efficient recruitment within an ongoing cohort, as well as prevention of disappointment bias and drop-out as control patients will not be informed about the trial.

**Trial registration:**

ClinicalTrials.gov NCT05575323. Registered on October 11, 2022.

## Administrative information

Note: the numbers in curly brackets in this protocol refer to SPIRIT checklist item numbers. The order of the items has been modified to group similar items (see http://www.equator-network.org/reporting-guidelines/spirit-2013-statement-defining-standard-protocol-items-for-clinical-trials/).

## Introduction

### Background and rationale {6a}

With improved cancer survival rates, more patients will develop bone metastases, with the spine as the most common site [1]. Spinal metastases increase the risk for pathological fracture, spinal cord compression, and spinal instability, which can lead to devastating consequences including progressive, unremitting pain, and paralysis. The disease burden is high and significantly impairs the patients daily functioning and health-related quality of life (HRQOL) [2, 3].

Radiotherapy is the standard of care for symptomatic spinal metastases and aims to relieve pain and to obtain local control of the tumor. In addition, in case of metastatic spinal cord compression or unstable spinal metastases, surgical stabilization with or without decompression may be required [4, 5]. Currently, radiotherapy is delivered after surgery as soon as the surgical wound is healed sufficiently, which is usually after a minimum time interval of one week. This time interval delays radiotherapy-induced pain relief, improvement of mobility and return to systemic oncological therapy.

Stereotactic body radiotherapy (SBRT) enables the delivery of high-dose radiation precisely to the spinal metastasis while keeping the dose to the spinal cord and surrounding tissues, including the surgical area, low [6, 7]. Post-operative SBRT with active dose sparing of the surgical site may reduce the risk of wound complications compared to conventional radiotherapy (cRT) [8]. This makes it possible to shorten or even eliminate the time interval between surgery and radiotherapy.

However, performing SBRT post-operatively is challenging. Accurate imaging (i.e., magnetic resonance imaging (MRI) and computed tomography (CT)) is required for the precise delivery of the ablative radiation dose to a spinal metastasis. Metallic spinal implants may cause imaging artifacts, preventing accurate identification of the neural structures to be avoided during radiation, and spinal implants may limit the dose behind implants [6, 9]. Also, as MRI is time consuming, it might be uncomfortable for patients to lay on their back for a long time in the post-operative setting. Therefore, patients may benefit from preoperative SBRT. In addition to a faster treatment response, another expected advantage is an accelerated continuation or start of systemic oncological therapy, including hormonal, immune, targeted, and chemotherapy, which could lead to earlier control of (other) metastases or the primary tumor.

By providing radiotherapy followed by surgery within a single hospital stay, patients may experience faster improvement of mobility, earlier pain relief, and faster restart of systemic oncological therapy. The benefits of having both treatments in a single hospital stay are substantial considering the often short life expectancy of these patients.

### Objectives {7}

The primary objective of this study is to evaluate the effectiveness of SBRT followed by surgical stabilization with or without decompression within 24 h compared with the standard of care, which is surgical stabilization with or without decompression followed by radiotherapy (either cRT or SBRT) as soon as the wound is healed sufficiently, in terms of physical functioning at four weeks after the start of the treatment.

Secondary objectives are as follows:To compare the pain response, duration of pain relief, length of hospital stay, time to return to systemic oncological therapy including hormonal, immune, targeted, and chemotherapy, neurological deterioration, adverse events (AEs) such as wound complications, HRQOL, and survival between the intervention and control group, andTo study the cost-effectiveness to assess whether same-day SBRT and surgery is cost-effective compared with the standard of care, from a societal perspective.

It is hypothesized that the same-day treatment procedure will result in faster recovery of mobility, less hospital visits, earlier pain relief from irradiation, and faster restart of systemic oncological therapy without an increase in wound complications due to the short interval between surgery and radiotherapy.

### Trial design {8}

The BLEND RCT is a phase III randomized controlled trial within the PRospective Evaluation of interventional StudiEs on boNe meTastases (PRESENT) cohort including patients referred to the radiotherapy or orthopedic surgery department of the University Medical Center (UMC) Utrecht for the treatment of bone metastases, according to the Trials within Cohorts (TwiCs) design [1, 10]. At cohort enrolment, patients are asked consent for collection of demographic and clinical data, and patient-reported outcomes, and for randomization into future intervention studies [11]. Patients are informed that they will be randomized to either the intervention or control arm when meeting the inclusion and exclusion criteria of a future trial. When allocated to the intervention arm, they will be offered the intervention which they can accept or refuse. Informed consent is obtained from those patients accepting the intervention. When allocated to the control arm, patients will not be notified about the trial and their cohort data will be used comparatively. Patients who meet the pre-specified in- and exclusion criteria for the BLEND RCT and who have provided informed consent for randomization into future trials will be randomly allocated 1:1 to the intervention or control arm. A flow chart of the study is presented in Fig. 1.

**Fig. 1 Fig1:**
[figure not shown]
Flow chart of the study. BLEND, Stereotactic Body radiotherapy and pedicLE screw fixatioN During one hospital visit for patients with symptomatic unstable spinal metastases; PRESENT, PRospective Evaluation of interventional StudiEs on boNe meTastases; SBRT, stereotactic body radiotherapy

## Methods: participants, interventions, and outcomes

### Study setting {9}

This study will be conducted within the UMC Utrecht, one of the largest academic healthcare institutions in the Netherlands, and will include patients that visit the multidisciplinary outpatient clinic of Radiation Oncology and Orthopedic Surgery.

### Eligibility criteria {10}

To be eligible, patients must meet the following inclusion criteria: (1) at least 18 years of age, (2) having symptomatic (cervical, thoracic and/or lumbar) spinal metastases from solid tumors and (impending) spinal instability requiring surgical stabilization (with or without decompression) and radiotherapy, (3) histologic proof of malignancy or radiographic/clinical characteristics indicating malignancy beyond reasonable doubt, (4) radiographic evidence of spinal metastases, (5) fit for (radio)surgery, (6) participation in PRESENT cohort, including consent for providing PROMs and randomization into future trials, and (7) written informed consent. Potential patients will be excluded when (1) SBRT cannot be delivered, (2) routine surgical stabilization with or without decompression and/or radiotherapy cannot be performed (e.g., multiple spinal metastases requiring surgical bridging of more than five vertebral levels and/or requiring radiotherapy on more than one location), (3) prior surgery or radiotherapy to the index level(s), (4) multiple myeloma, (5) neurological deficits (American Spinal Injury Association (ASIA) impairment scale grade A, B, or C) or partial neurological deficits (ASIA grade D) with rapid progression (hours to days), (6) current treatment with Bevacizumab and other medication with long half-life that interferes with radiotherapy, (7) life expectancy of less than 3 months, and/or (8) pregnancy.

### Who will take informed consent? {26a}

Patients will be informed at the outpatient innovation clinic by the research team about the PRESENT cohort. Patients are asked informed consent for the collection of demographic and clinical data and patient-reported outcome measures (PROMs) at regular time points. Patients can provide additional consent for randomization into future intervention studies (i.e., broad consent) [11]. Patients who provided broad consent and who meet the eligibility criteria will be randomly allocated 1:1 to the intervention or control arm stratified by renal cell carcinoma versus other primary tumor histologies. Patients allocated to the intervention arm will be offered the intervention, which they may accept or refuse. Upon acceptance, informed consent will be obtained by a member of the research team.

### Additional consent provisions for collection and use of participant data and biological specimens {26b}

Not applicable, no additional samples will be collected.

### Interventions

#### Explanation for the choice of comparators {6b}

According to the TwiCs design, the control group will receive standard of care. Current standard of care is surgical stabilization with or without decompression followed by radiotherapy (either cRT or SBRT) as soon as the wound is healed sufficiently, which is usually after a minimum time interval of 1 week. Inherent to the TwiCs design, control patients will not be informed about the trial and that they serve as a control. Previous research showed that most patients were positively or neutrally to having served as controls without notification of being selected for the control group [12]. By not informing controls, disappointment bias and contamination (i.e., control patients receiving the experimental intervention) may be prevented.

#### Intervention description {11a}

Patients who accept the intervention will receive same-day SBRT and surgery. Before treatment, patients will undergo an extended MRI and CT scan in treatment position for planning purposes. Next, cone beam CT (CBCT) before and during dose delivery is made to correct for position deviations. Then, patients will receive SBRT, which will be a single high dose of at least 18 Gray (Gy); this dose can be increased to 21 Gy in patients with radioresistant tumors, to the affected vertebra. Dose constraints are set for the organ at risks based on institution specific guidelines. Within 24 h after SBRT, surgical stabilization with or without decompression will be performed according to the standard of care and on an elective base. The type of (pedicle screw) fixation will be decided by the surgeon depending on the need for surgical decompression, vertebral levels to be included in the construct, and the bone quality.

The control arm and patients who refused to undergo the intervention will receive the standard of care. Currently, the standard of care for patients with unstable spinal metastases is surgical stabilization with or without decompression followed by cRT or SBRT as soon as the surgical wound has healed sufficiently. Before surgery, all patients will undergo an extended planning MRI in radiotherapy treatment position. After surgery and before radiotherapy, when the wound is healed sufficiently, a planning CT is made and another MRI to see if the neurological structures have moved after surgery. Pre- and postoperative MRI are mutually registered to yield information on all relevant structures for planning assessing dose distribution using volumetric modulated arc therapy (VMAT). Also, CBCT data will be acquired to correct for translations or rotations, and if correct in subsequent CBCTs, radiotherapy will be delivered.

#### Criteria for discontinuing or modifying allocated interventions {11b}

If it turns out that patients do not meet the inclusion criteria after randomization (e.g., proper planning of the radiation dose is not possible without meeting the constraints to the organs at risk, especially the spinal cord), patients will be excluded from the BLEND RCT and they will receive standard of care. The intervention or standard of care can be discontinued or modified for urgent medical reasons. Patients can withdraw consent for the intervention and/or participation in the PRESENT cohort (and hence the BLEND RCT) at any time for any reason if they wish to do so without any consequences.

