**Enrolment**									
Informed consent PRESENT cohort	X								
Eligibility screening BLEND RCT	X								
Randomization BLEND RCT	X								
Informed consent BLEND RCT (upon acceptance of intervention)		X							

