#### Implementation {16c}

The research team will screen patients on eligibility. If a patient appears eligible, the research team will perform online randomized allocation.

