#### Methods in analysis to handle protocol non-adherence and any statistical methods to handle missing data {20c}

Analysis will be based on the intention-to-treat principle. However, in accordance with the TwiCs design, patients who are selected for the intervention arm may refuse the intervention. In case of a high refusal rate (i.e., > 15%), we will also conduct a per protocol (PP) analysis including patients who completed the treatment as allocated. However, refusal may be selective, e.g., patients who are less physically fit may refuse the intervention. As a result, PP analysis may under- or overestimate the treatment effect. We will also perform a complier average causal effect (CACE) analysis to estimate the treatment effect among “compliers,” i.e., patients that accepted and received the intervention offered compared with hypothetical control patients who, if offered the intervention, would have accepted.

In the palliative oncology setting, questionnaire non-response is more likely due to inability to complete questionnaires as a result of for example fatigue and high distress or filling in questionnaires may be too burdensome. The proportion and patterns of missing data for the primary and secondary outcomes will be investigated. If needed, multiple imputation methods will be used to handle missing data under the assumption that data is missing at random. If the primary outcome data is determined to be missing not at random, a best–worst and worst-best case sensitivity analyses will be performed.

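### Exclusion after randomisation for a failed radiation plan will fall mainly on the intervention arm and conflicts with the stated intention-to-treat analysis

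*Protocol article*

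**What the plan says.** All references are to the protocol article.

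- **Exclusion rule.** Section {11b} covers patients found after randomisation not to meet the criteria: "patients will be excluded from the BLEND RCT and they will receive standard of care". The example given is that "proper planning of the radiation dose is not possible without meeting the constraints to the organs at risk, especially the spinal cord". This corresponds to the first exclusion criterion in {10}: "Potential patients will be excluded when (1) SBRT cannot be delivered".
- **Timing of allocation.** Under {16c}, "If a patient appears eligible, the research team will perform online randomized allocation". The participant timeline {13} places the row "Randomization BLEND RCT" before the first consultation with the radiation oncologist and orthopaedic surgeon.
- **Planning.** In {11a}, patients who accept the intervention have a planning MRI and CT before treatment. Standard-care patients have a planning MRI before surgery, but their CT comes later: "After surgery and before radiotherapy, when the wound is healed sufficiently, a planning CT is made". A second MRI is made at that point to see whether neurological structures have moved. Their radiotherapy may be conventional or SBRT.
- **Blinding.** Section {17a} states that researchers and clinicians cannot be blinded.
- **Analysis set.** Section {20c} says "Analysis will be based on the intention-to-treat principle", and {20a} says the same of the primary comparison. Neither section mentions the {11b} exclusions. The provision in {18b} for continued use of cohort data is written for patients who withdraw, not for patients who are excluded.

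**The concern.** Intention-to-treat protects the comparison because everyone randomised is analysed in the arm to which they were allocated. The {11b} rule removes patients on information that comes from preparing the experimental treatment, after allocation is known. A control patient with the same anatomy has no preoperative SBRT plan that could fail, and so stays in.

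If patients whose plan fails differ in expected physical functioning from the others, the trimmed intervention arm is no longer comparable with the complete control arm. The primary 4-week contrast then carries that difference. The CACE analysis in {20c} is exposed to the same problem, because it relies on the randomised arms being comparable before receipt of treatment is considered.

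**Working it through.** **1. Is the exclusion one-sided?** Four statements, read together:

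- Allocation precedes planning ({16c} and the timeline), so a failed plan is always post-randomisation information.
- The preoperative planning CT for SBRT is described only for acceptors ({11a}).
- A control who is planned for SBRT is planned after surgery, on possibly altered anatomy. Conventional radiotherapy is also within standard care, so a failed SBRT plan need not come to light as ineligibility.
- Moving an excluded patient to standard care changes something only for an intervention patient, since controls already receive it.

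The trimming is therefore mainly, though not exclusively, in the intervention arm.

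**2. The plan's own sample size.** Inputs from {14}: difference 13, SD 22, two-sided α 5%, power 80%.

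n per arm = 2 × [22 × (1.960 + 0.842) / 13]² = 44.96, rounded up to 45. The 10% increase gives 45 / 0.9 = 50 per arm, 100 in total. The stated figures reproduce. The allowance is for refusal, questionnaire nonresponse and dropout; post-randomisation exclusion is not listed.

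**3. Bias if patients are excluded as written.** Let f be the fraction of the intervention arm removed and d the number of points by which the removed patients score below those kept. The trimmed mean exceeds the full-arm mean by f × d. The documents give neither quantity, so f = 5–20% and d = 5–20 points are assumptions. If the removed patients score higher, the sign reverses.

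Type I error uses the normal approximation with SE = 22 × √(1/50 + 1/[50(1 − f)]). For f = 10% and d = 10, the bias is 0.10 × 10 = 1.0 point, SE = 22 × √(1/50 + 1/45) = 4.52, and the two-sided type I error is 5.6%.

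| f | Bias, d = 5 to 20 (points) | Two-sided type I error |
|---|---|---|
| 5% | 0.25–1.0 | 5.0–5.6% |
| 10% | 0.5–2.0 | 5.1–7.3% |
| 15% | 0.75–3.0 | 5.3–10.0% |
| 20% | 1.0–4.0 | 5.5–13.8% |

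These figures are for an unadjusted comparison with SD 22.

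**4. Cost of keeping everyone.** If plan failures stay in and gain nothing, the expected effect is 13 × (1 − f). With 50 analysed per arm, SE = 22 × √(2/50) = 4.4. For f = 10%, 11.7 / 4.4 − 1.96 = 0.70, which gives power of 75.8%. With f = 0 the same formula gives about 84%.

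| f | Effect (points) | Power, 50 analysed per arm | Analysed per arm for 80% power |
|---|---|---|---|
| 5% | 12.35 | 80.1% | 50 |
| 10% | 11.7 | 75.8% | 56 |
| 15% | 11.05 | 70.9% | 63 |
| 20% | 10.4 | 65.7% | 71 |

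**The case against.** The strongest defence is that the rule is not written for one arm and the harm may be small. Section {11b} speaks of patients generally, and ineligibility of other kinds could surface in either arm. Controls have a preoperative planning MRI and may receive SBRT. Inability to deliver SBRT is also an exclusion criterion screened before allocation, so some unsuitable patients leave before either arm is formed. All of this stands. A reader might infer that plan failure can be found only in the intervention arm; the documents support mainly, not only. A reader might also infer that controls usually receive conventional radiotherapy. Only the abstract says so, whereas the objectives, comparator, intervention and discussion sections allow either type.

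On direction, a reader might infer that patients with tumour near the cord function worse, so that their removal favours same-day SBRT. That is plausible, but no section shows it. The neurological exclusions in {10} (ASIA grades A to C, and D with rapid progression) apply to both arms and may narrow any gap.

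On size, {20a} adjusts for baseline physical functioning, age, Karnofsky score and medication use. Only the part of the gap not explained by these covariates biases the adjusted estimate, so the raw figures are too large to the extent that the covariates explain it.

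None of this reconciles {11b} with {20a} and {20c}. Adjustment reduces the bias but does not restore the randomised comparison.

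**Conclusion.** The concern holds as a conflict within the protocol. Followed literally, {11b} removes randomised patients mainly from one arm, on information produced by preparing the experimental treatment and judged by unblinded staff, while {20a} and {20c} promise intention-to-treat.

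The primary comparison and the CACE estimate may be biased. The direction cannot be settled from the documents. The size rests on two assumed inputs: 0.25–4.0 points unadjusted over the ranges shown (1.0 point at 10% and 10 points), and less to the extent that the covariates account for the gap. If plan failures are rare or have a similar prognosis, the effect is small.

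Two stronger readings go too far. A reader might infer that the CACE analysis is invalidated; it may be biased, by an amount that depends on the same unknowns, but invalidity is not shown. A reader might also infer that refusers are excluded, because {10} ends its inclusion list with "and (7) written informed consent" and refusers sign no trial-specific consent. Section {11a} gives refusers standard care, and {20c} plans its analyses around refusal. The same literal reading would also disqualify every control. That criterion is loosely worded, a minor drafting matter that is not part of this point.

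**What to change.** Reconcile {11b} with {20a} and {20c} as follows:

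- State that patients found unsuitable for SBRT after randomisation remain in the intention-to-treat analysis in their allocated arm, using their PRESENT outcomes, and count as not having received the intervention in the CACE analysis.
- Allow post-randomisation exclusion only on information dated before randomisation, judged without knowledge of the arm and applied alike to both arms.
- Extend the follow-up provision in {18b} so that it covers these patients as well as withdrawals. Recruitment began in November 2022, so apply the rule also to anyone already excluded on this ground.

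Patient care does not change, and PRESENT already collects the outcomes. The cost is a diluted intention-to-treat effect. If 10% are plan failures with no benefit, the expected difference falls from 13 to 11.7 points, power with 50 analysed per arm is about 76%, and 56 analysed per arm would be needed for 80%. The power statement in {14} should be qualified accordingly. The interim look in {21b}, which already allows the sample size to be revisited, is a natural point to review the number of plan failures.
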